**Methods:**

This will be a multicenter, randomized, double-blind, double-dummy, placebo-controlled, parallel group trial involving six Australian and New Zealand centers. In total, 170 eligible children will be stratified by site and bronchiectasis etiology, and randomized (allocation concealed) to receive: 1) azithromycin (5 mg/kg daily) with placebo amoxycillin-clavulanate or 2) amoxycillin-clavulanate (22.5 mg/kg twice daily) with placebo azithromycin for 21 days as treatment for non-severe respiratory exacerbations. Clinical data and a parent-proxy cough-specific quality of life (PC-QOL) score will be obtained at baseline, at the start and resolution of exacerbations, and on day 21. In most children, blood and deep-nasal swabs will also be collected at the same time points. The primary outcome is the proportion of children whose exacerbations have resolved at day 21. The main secondary outcome is the PC-QOL score. Other outcomes are: time to next exacerbation; requirement for hospitalization; duration of exacerbation, and spirometry data. Descriptive viral and bacteriological data from nasal samples and blood inflammatory markers will be reported where available.

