Although most respiratory physicians will treat acute exacerbations intensively with antibiotics and airway clearance [24,30], some exacerbations are caused by viral infections, and may not require antibiotic therapy. However, it is possible that viral-bacterial interactions in the airways could promote or prolong endobronchial bacterial infection, which, with the accompanying inflammatory cascade, is a risk for additional lung injury [26,31]. To address whether antibiotics are superior to placebo at providing short-term clinical benefits, the first component of our Bronchiectasis Exacerbation Study (BEST), is a multicenter randomized controlled trial (RCT; BEST-1) designed to answer the question: ‘Does azithromycin or amoxycillin-clavulanate, compared with placebo, improve the resolution of respiratory exacerbations on day 14 of treatment?’ [32].

The second component of BEST (BEST-2) seeks to determine whether the two antibiotics used in BEST-1 are equivalent at achieving resolution of an acute respiratory exacerbation in children with bronchiectasis, compared with placebo. Based on available, but limited, data on the microbiology of lower-airway secretions in children with non-CF bronchiectasis [33], amoxycillin-clavulanate is currently recommended as the first-line empirical oral-antibiotic treatment for non-severe bronchiectasis exacerbations in children [24]. However, amoxycillin-clavulanate requires dosing two to three times per day, and causes gastrointestinal symptoms in many children. Oral azithromycin is attractive as an alternative first-line therapy because of its long half-life, markedly reduced dosing schedule, and good safety profile in children [34]. Although azithromycin can be used 3 days/week [35] or even once weekly [36], our proposed study uses a daily dose in order to maintain effective blinding of the medications. However, if daily azithromycin is shown to be equivalent to amoxicillin-clavulanate, then extended-interval azithromycin dosage schedules could be trialed in appropriate clinical settings where reduced dosing frequency is particularly appealing, such as for patients likely to have poor adherence.

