### Intervention and follow-up

A double-dummy design is planned. If eligibility is fulfilled, and after informed consent has been obtained, the child will be randomized to one of two arms. At the start of the exacerbation, the child will receive orally: 1) azithromycin with placebo amoxycillin-clavulanate or 2) amoxycillin-clavulanate with placebo azithromycin. The azithromycin dose is 5 mg/kg/day (to a maximum of 200 mg daily, and for amoxycillin-clavulanate it is 22.5 mg/kg/dose twice daily (maximum 900 mg/dose). Equivalent volumes of placebo will be given for both trial medications. All treatments will continue for 21 days.

An exacerbation is defined as an increase in sputum volume or purulence, or change in cough (>20% increase in cough score [46] or type (dry to wet) [47]) for more than 3 days. We validated this definition in our prospective study, and found that the kappa values (between clinicians) of these symptoms and signs were excellent (>0.75) [48]. Daily diaries will also be collected during exacerbations until the scores for 2 or more days reflect the child’s baseline state, which for each child will be established at enrolment, prior to any exacerbations. This assessment consists of a combination of symptoms (daily cough (yes/no), cough quality (wet/dry/none), cough score [46] averaged over two consecutive days) and signs (sputum color (if any present) using a color chart card (BronkoTest Ltd, London, UK), and crackles on chest auscultation). Children will be reviewed on days 14 and 21, and at resolution of the exacerbation. The exacerbation is considered resolved when symptoms and signs are the same as the baseline state. Post-exacerbation, the children will be followed up and evaluated clinically every 3 months for a period of 18 months or until their next exacerbation (whichever is sooner). The time to next exacerbation will be determined by duration of days from the resolution of the current exacerbation to the beginning of the next exacerbation.

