### End points

Participation will be complete when the child’s clinical state returns to baseline and the time to next exacerbation has been obtained. Other exit points are: if the child deteriorates during treatment prior to day 21, or becomes sufficiently intolerant of the trial medications to require withdrawal from the study (as determined by the treating clinician).

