### Outcome measures

#### Primary outcome

The primary outcome will be the proportion of children whose exacerbations have resolved by day 21 of treatment. Exacerbations will be considered resolved when symptoms and signs are the same as the baseline state. Children who are withdrawn from the study, or receive additional antibiotic treatment, will be categorized as non-resolved.

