### Statistical analysis and reporting

Data will be reported and presented in accordance with the updated Consolidated Standards of Reporting Trials (CONSORT) criteria [66]. Children will be analyzed in accordance with allocation status (regardless of subsequent management).

For our primary aim, the main effects of the interventions will be determined by comparing the primary outcome (resolution of exacerbation) between groups (azithromycin versus amoxicillin-clavulanate). Children who exit the study as ‘clinically worse’ or ‘drop-out’ before the end point is reached will be considered as ‘non-resolved’. Those who exit the study as ‘returned to baseline’ will be considered as ‘resolved’. Odds ratios will be calculated and, if appropriate, the number needed to treat (for benefit) will be expressed. Per-protocol analysis will be an *a priori* secondary analysis.

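### The Primary outcome and Statistical analysis sections code withdrawals by different rules, and neither fixes the order of events relative to resolution

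*Protocol article*

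**What the plan says.** Four parts of the protocol article bear on how the primary outcome is coded.

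- **Primary outcome.** The endpoint is a proportion: "The primary outcome will be the proportion of children whose exacerbations have resolved by day 21 of treatment". Resolution means that symptoms and signs match the baseline state. An override follows: "Children who are withdrawn from the study, or receive additional antibiotic treatment, will be categorized as non-resolved".
- **Statistical analysis and reporting.** Children who leave as clinically worse or as drop-outs "before the end point is reached will be considered as" non-resolved. The success limb reads "Those who exit the study as ‘returned to baseline’ will be considered as ‘resolved". Additional antibiotics are not mentioned.
- **Abstract, Methods.** The endpoint is worded as a status on a given day: "The primary outcome is the proportion of children whose exacerbations have resolved at day 21".
- **Intervention and follow-up, and End points.** Dosing does not stop at recovery: "All treatments will continue for 21 days". A child may exit who "becomes sufficiently intolerant of the trial medications to require withdrawal from the study". Participation is complete only when the child is back at baseline and the time to next exacerbation is known. Follow-up runs for up to 18 months or until that exacerbation.

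On tolerability, the Background says that "amoxycillin-clavulanate requires dosing two to three times per day, and causes gastrointestinal symptoms in many children" and describes azithromycin as having a good safety profile in children. No rate is given for either drug.

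**The concern.** The override and the analysis rule can give opposite codes to a child whose return to baseline is already documented. Such children are foreseeable: those who recover early stay on trial medicine to day 21 and in follow-up after that, so withdrawal or another antibiotic can come after resolution.

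The direction of any error matters in a non-inferiority trial. Counting withdrawals as failures looks conservative, but lowering the comparator's success rate helps the test drug. If intolerance after recovery is more common on amoxycillin-clavulanate, as the Background makes plausible, the override would remove true resolutions from the comparator and move the result toward non-inferiority. The double-dummy design does not prevent this, because each child takes only one active drug. If the choice between the rules were made after the data are seen, the primary result would be weakened.

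**Working it through.** **Step 1: the two rules side by side.** Each test child is back to baseline on day 10.

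| Later event | Primary outcome section, read literally | Statistical analysis section |
|---|---|---|
| Withdrawn for intolerance on day 13 | Non-resolved | Resolved if the exit is labelled as returned to baseline; non-resolved if it is labelled a drop-out before the end point |
| Antibiotic for an unrelated infection on day 17 | Non-resolved | Silent |
| Antibiotic during later follow-up | Non-resolved (no time limit) | Silent |

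Row 1 is a conflict that depends on a label, and no section says how to label an intolerant child who is already at baseline. Rows 2 and 3 are not contradictions. They show a rule without a limit on time or indication.

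The Abstract's wording adds to the ambiguity. If the endpoint is status *at* day 21, the row 1 child has a missing outcome. If it is resolution *by* day 21, the outcome is known and is overwritten.

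**Step 2: the plan's own figure.** Inputs from Sample size: 80% resolution (taken as equal in both arms), 20-point margin, 90% power, 85 per arm.

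n per arm = (z₁₋α + z₁₋β)² × [0.8×0.2 + 0.8×0.2] / 0.20²

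- One-sided 0.025: (1.960 + 1.282)² × 0.32/0.04 = 84.1, so 85 per arm, 170 in total. This matches.
- One-sided 0.05, as printed: (1.645 + 1.282)² × 0.32/0.04 = 68.5, so 69 per arm, 138 in total. This does not match.

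The mismatch in alpha is a separate matter. Step 4 therefore shows both levels.

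**Step 3: size per child.** One recoded child moves that arm's rate by 1/85 = 1.2 points. Five recoded comparator children turn 68/85 = 80.0% into 63/85 = 74.1%, which is 5.9 of the 20 margin points.

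**Step 4: effect on the error rate.** Assume true resolution exactly at the margin: comparator 80%, azithromycin 60%. Let f_C and f_A be the assumed shares of resolved children recoded as failures. The observed rates become 0.80(1 − f_C) and 0.60(1 − f_A). Non-inferiority is claimed when the lower Wald bound for azithromycin minus comparator exceeds −20 points. Probabilities come from exact binomial enumeration with 85 per arm.

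| f_C v f_A | Observed rates (comparator v azithromycin) | Difference, points | False claim, one-sided 0.05 | One-sided 0.025 |
|---|---|---|---|---|
| 0 v 0 | 80.0% v 60.0% | −20.0 | 5.1% | 2.5% |
| 2% v 5% | 78.4% v 57.0% | −21.4 | 3.3% | 1.5% |
| 5% v 5% | 76.0% v 57.0% | −19.0 | 6.6% | 3.4% |
| 5% v 2% | 76.0% v 58.8% | −17.2 | 10.7% | 5.8% |
| 10% v 2% | 72.0% v 58.8% | −13.2 | 23.9% | 15.1% |

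The documents supply none of these shares. Equal recoding shrinks the absolute difference slightly. Only an excess in the comparator gives large inflation, and an excess on azithromycin makes the test conservative.

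**The case against.** - **The sections can be read together.** The Primary outcome section never says that a resolved child becomes a failure; it is silent on order. Its first sentence may be meant to limit everything to day 21, with the Statistical analysis section as the working version. That is a fair reading and perhaps the intended one, but it has to be inferred. Even with a day-21 limit, the day-13 withdrawal stays unsettled.
- **A reader might infer that the two sections also contradict each other on additional antibiotics.** They do not, because the Statistical analysis section says nothing on the subject. What stands is that the override has no limit on time or indication. A full protocol or analysis plan might define the indication.
- **A reader might infer that the override falls mainly on the comparator arm.** The documents do not support that as a fact. The Background makes it plausible for intolerance withdrawals only, and no withdrawal rates are given. Additional antibiotics could fall more on azithromycin if it were the weaker drug.
- **Composite endpoint.** Resolution without withdrawal or additional antibiotics is a recognised endpoint, and against it the recoding is not an error. This stands as a legitimate choice, but the protocol would have to state it consistently, and its success limb for exits at baseline points the other way. The planned per-protocol analysis does not settle the coding of the primary one.

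**Conclusion.** The point holds as an inconsistency in the coding of the primary outcome. For withdrawal after documented return to baseline, the two sections can give opposite answers, and the answer turns on an exit label that is not defined. For additional antibiotics the defect is an unbounded rule. The wording at day 21 against by day 21 makes both harder to resolve.

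Bias toward non-inferiority is possible, not shown. In the assumed cases the false-claim rate at one-sided 0.05 ranges from 3.3% to 23.9%, against 5.1% without recoding. Both the sign and the size rest on the assumed recoding shares. The figures also assume a Wald interval, true rates of 80% and 60%, and resolution by day 21 as the intended target. The ambiguity should be settled before unblinding, because it concerns the primary endpoint and costs little to remove.

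**What to change.** Replace the two passages with one coding rule, set before unblinding, and use the same day-21 wording throughout, including the Abstract. The rule should:

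1. limit the override to events on or before day 21;
2. code withdrawal before documented return to baseline as non-resolved;
3. keep a child with documented return to baseline before withdrawal as resolved, which agrees with resolution by day 21 and with the Statistical analysis section;
4. state whether antibiotics for unrelated indications count.

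Report the unconditional coding in the Primary outcome section as a sensitivity analysis. These are changes to outcome coding only; they do not touch treatment or withdrawal decisions.

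The cost is a few sentences in the protocol or analysis plan, dates of resolution, withdrawal and antibiotic start, and one field for the antibiotic's indication. The downside is that someone must classify that indication, which can be done blinded.

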### Aims of the study

In the second phase of BEST (BEST-2) the primary question will be: ‘Is daily oral azithromycin non-inferior (within a 20% margin) to oral amoxycillin-clavulanate at achieving resolution of exacerbations by day 21 of treatment?’

The secondary aims are similar to those in BEST-1 [32], and are to: 1) determine the effect of azithromycin or amoxycillin-clavulanate on QOL, systemic inflammation, time to next respiratory exacerbation, and duration of exacerbations; 2) examine factors that predict response to the two antibiotics, including respiratory pathogens (viruses, bacteria, macrolide-resistant bacteria) present in respiratory secretions, and systemic markers of inflammation; and 3) describe, by using sensitive molecular detection techniques, the point prevalence and diversity of respiratory viruses and *Mycoplasma pneumoniae* and *Chlamydiales* species during exacerbations, compared with the findings at enrolment when the children are clinically stable.

The study will test the primary hypothesis that oral azithromycin is non-inferior (within a 20% margin) to oral amoxycillin-clavulanate at achieving resolution of respiratory exacerbations by day 21 of treatment in children with non-CF bronchiectasis.

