### Sample size

We plan to enroll 170 children (85 per arm), providing 90% power (α = 0.05, 1-sided) with 20% non-inferiority margin to detect 80% resolution rate by day 21. The margin selected is relatively large in statistical terms, but the physicians considered it clinically appropriate. As the primary outcome will be obtained in all enrolled children, retention fraction has not been factored in for the intention-to-treat analysis.

The main secondary outcome (secondary aim 1) is PC-QOL. Based on a non-inferiority limit of 0.9 (minimum important difference [57]) and standard deviation of 0.9, our sample size provides a power of 99.9% (α = 0.05, one-sided 95% CI) for data from at least 136 children (assuming at least 80% retention of children enrolled). For secondary aim 2 (see list under ‘Aims of the study’), we will be examining eight main factors, and thus a sample size of 136 exceeds the recommended minimum (n = 10 per factor) [65]. The eight factors are: smoking, age, underlying etiology, detection of virus (any versus none, then single versus multiple viruses), presence of azithromycin resistance, and levels of various blood markers (IL-6, IL-10, IP-10).

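### Counting drop-outs as non-resolved, with per-protocol analysis only secondary, can favour a non-inferiority claim if outcome-unrelated loss is material and not concentrated on azithromycin

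*Protocol article*

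**What the plan says.** The primary hypothesis (Aims of the study) is non-inferiority of azithromycin within a 20% margin for resolution by day 21. Four statements in the protocol article bear on exits from the study.

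- **Primary outcome:** "Children who are withdrawn from the study, or receive additional antibiotic treatment, will be categorized as non-resolved". No reason for withdrawal is distinguished.
- **Statistical analysis and reporting:** children who leave clinically worse and children who drop out are listed as two separate groups, and both count as non-resolved. Children who leave having returned to baseline count as resolved. Analysis follows allocation, whatever the later management.
- **Same section:** "Per-protocol analysis will be an *a priori* secondary analysis". Nothing says that it must agree with the allocation-based result before non-inferiority is concluded.
- **Sample size:** "As the primary outcome will be obtained in all enrolled children, retention fraction has not been factored in for the intention-to-treat analysis". For the quality-of-life outcome (PC-QOL), the same section works with 136 children, "assuming at least 80% retention of children enrolled".

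Timing also matters. Under Randomization, allocation, and blinding, a child receives a number on the stratified list at enrolment. Under Intervention and follow-up, trial medication is given only when an exacerbation begins.

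**The concern.** In a superiority trial, counting every lost child as a failure is usually cautious. In a non-inferiority trial it can work the other way. If a share of each arm is set to failure regardless of what would have happened, the observed difference is the true difference multiplied by the share that remains, so a real deficit looks smaller.

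Failure coding is defensible for a child who deteriorates, cannot tolerate the medication or needs further antibiotics. The rule also reaches children who leave for reasons unconnected with the outcome. Because randomization precedes treatment, one such group is easy to foresee: children who withdraw after enrolment but before any treated exacerbation. Read literally, they are randomized, untreated and non-resolved. Their loss cannot depend on a blinded drug they never took, so it should be roughly balanced, which is the pattern that dilutes.

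At stake is the error rate of the analysis that decides the trial. The article itself calls the margin relatively large, and no other stated analysis has a say in the conclusion.

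**Working it through.** **Inputs.** From Sample size: 85 per arm, margin 20 points (read as an absolute risk difference), 80% resolution, one-sided alpha 0.05, 90% power. Assumed: drop-out d from 0 to 20%, unrelated to outcome. The article gives no drop-out rate for the primary outcome.

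**The plan's own figure.** n per arm = (0.8×0.2 + 0.8×0.2) × (z_alpha + z_power)² / 0.20².

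- One-sided 0.05: 0.32 × (1.645 + 1.282)² / 0.04 = 68.5, so 69 per arm.
- One-sided 0.025: 0.32 × (1.960 + 1.282)² / 0.04 = 84.1, so 85 per arm, with 90.3% power.
- One-sided 0.05 with variance at the margin (80% and 60%): 0.40 × (1.645 + 1.282)² / 0.04 = 85.6.

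The planned 85 is thus matched by standard variants, but not by the literal inputs with 80% in both arms. Results are given at both alpha levels.

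**False claim at the margin, balanced loss.** True rates are 80% (control) and 60% (azithromycin). With failure coding the analysed rates are 0.8(1-d) and 0.6(1-d), and the analysed difference is 0.20(1-d). The normal approximation is

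P(claim) = Phi{[0.20 - 0.20(1-d)] / SE - z}, SE = sqrt{[pc(1-pc) + pt(1-pt)] / 85}.

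At d = 20%: pc = 0.64, pt = 0.48, SE = sqrt(0.48/85) = 0.0751. Then 0.04/0.0751 - 1.645 = -1.11, giving 13.3%. Exact binomial enumeration of the Wald limit gives:

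| d | analysed rates | difference | false claim, 5% | false claim, 2.5% |
|---|---|---|---|---|
| 0% | 80 v 60 | 20 points | 5.1% | 2.5% |
| 5% | 76 v 57 | 19 points | 6.6% | 3.4% |
| 10% | 72 v 54 | 18 points | 8.2% | 4.4% |
| 15% | 68 v 51 | 17 points | 10.5% | 5.8% |
| 20% | 64 v 48 | 16 points | 13.3% | 7.8% |

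If only children with an observed outcome are analysed, and loss is unrelated to outcome, the rate stays near 5% or 2.5% at every d.

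**Unbalanced loss (one-sided 5%).**

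| control loss | azithromycin loss | difference | false claim |
|---|---|---|---|
| 10% | 5% | 72 - 57 = 15 points | 16.7% |
| 20% | 10% | 64 - 54 = 10 points | 37.7% |
| 5% | 10% | 76 - 54 = 22 points | 2.6% |
| 10% | 20% | 72 - 48 = 24 points | 1.3% |

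Break-even is where 0.8 × control loss = 0.6 × azithromycin loss, that is, azithromycin loss = 1.33 × control loss.

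**If the drugs are equal at 80%.** The same coding lowers power. At d = 20% it falls from 94.8% to 85.7% (one-sided 5%), or from 90.3% to 77.4% (2.5%).

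**The case against.** The strongest reply is that the loss may be trivial. The article expects the primary outcome in all enrolled children, treatment lasts 21 days, and the early exits named under End points are deterioration and intolerance, where failure coding is reasonable. At 5% outcome-unrelated loss the false-claim rate is 6.6% against 5.1%, a modest change. This stands as a limit on size. It does not remove the point, because the expectation of full ascertainment rests partly on the coding rule itself, which supplies an outcome for any child who leaves, and because enrolment comes before treatment.

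Several stronger readings are tempting and are not supported:

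- **That the plan expects 20% loss on the primary outcome.** The 80% retention figure belongs to PC-QOL. Here it is only the upper end of an assumed range.
- **That every exit counts as failure.** Exits at baseline state count as resolved. Coding additional antibiotics as failure tends to preserve a difference that such treatment would otherwise mask.
- **That the rule always favours non-inferiority.** The direction depends on the drop-out pattern, and under true equality the rule works against the claim.
- **That control-arm intolerance proves a large bias.** The Background says the control causes gastrointestinal symptoms in many children, so more control exits are plausible. Those exits are intolerance, however, and counting them as failure is a recognised composite outcome. The 16.7% and 37.7% figures apply only to excess control loss unrelated to outcome.
- **That per-protocol analysis is missing, or would be unbiased.** It is pre-specified, and exclusions after randomization bring their own bias. The case is for agreement between the two analyses, not for replacing one with the other.

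Technical detail of imputation is normally left to an analysis plan, and its absence from an article is not a fault. The coding rule and the ranking of the analyses, however, are fixed in the article.

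**Conclusion.** The point holds conditionally. As written, the rule counts outcome-unrelated drop-outs as non-resolved in the deciding analysis, and per-protocol analysis has no stated part in the conclusion. If such loss is material and roughly balanced, or higher on control, the false non-inferiority rate exceeds its nominal level: 8.2% at 10% balanced loss and 13.3% at 20%, against 5.1% with none (4.4% and 7.8% against 2.5% at one-sided 2.5%).

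This rests on true rates of 80% and 60%, 85 per arm, a Wald limit on the absolute difference, and assumed loss rates. With near-zero loss the effect is negligible, and with azithromycin loss above about 1.33 times control loss it reverses. It is a worthwhile and inexpensive improvement, not evidence that the planned analysis must mislead.

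**What to change.** 1. Keep failure coding for deterioration, intolerance and additional antibiotics, and keep exits at baseline state as resolved.
2. State that non-inferiority is concluded only if the confidence intervals for the risk difference (azithromycin minus control) in both the allocation-based and the per-protocol analyses exclude -20 points.
3. Pre-specify a sensitivity analysis, by multiple imputation or tipping point, for drop-outs unrelated to outcome. Say explicitly how it treats children who leave after randomization but before any treated exacerbation.

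**Cost.** Wording and extra analysis, no new data, and some power. Suppose the per-protocol set is 68 per arm (80% of 85) with 80% resolution in both arms. Then SE = sqrt(0.32/68) = 0.0686, and that comparison alone has power Phi(0.20/0.0686 - 1.645), about 90%, at one-sided 5%, or Phi(0.20/0.0686 - 1.960), about 83%, at 2.5%. The power of the joint requirement is at or below the lower of its two components. If the other 17 children per arm are all outcome-unrelated drop-outs coded as failures, the lower component is the allocation-based analysis, at 85.7% or 77.4%.
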